# Objectives

1. Describe the purpose, specific aims, or objectives of the study (i.e. the reason for performing the study in terms of the scientific question to be answered):

The aim of this study is to evaluate the accuracy of the KOSMOS portable ultrasound automated LVEF, stroke volume, and cardiac output detection in a real-world, clinical setting. We hypothesize that automated results will demonstrate a strong correlation with formal TTE and right heart catheterization studies.

- The primary outcome of interest is the overall diagnostic accuracy of the automated LVEF, stroke volume, and cardiac output computation as compared to either TTE (for LVEF assessments) or right heart catheterization (for stroke volume and cardiac output assessments).
- The secondary outcome of interest is time to LVEF acquisition with FoCUS

#

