### D.4.1 Local Recruitment Methods

Describe the following attributes of the recruitment plan for the local Tufts site:

1. When, where, and how potential subjects will be recruited:

Potential subjects will be screened for potential recruitment by the study investigators This will occur when patients are admitted to the inpatient medical, surgical or intensive care units at Tufts Medical Center and/or when they present to TMC for an echocardiogram and/or right heart catheterization. Once screened for possible inclusion the study team will approach the patient for inclusion in the study.

1. Source of subjects (for example, patient population, local community, etc.): Subjects presenting to TMC for an echocardiogram and/or right heart catheterization and those admitted to TMC.
2. Methods that will be used to identify potential subjects: Physician referral and chart review
3. If print and media advertisements will be used, specify when, where, how long and frequency of the advertisements that will be published/aired:       or  N/A
   1. Check to confirm that any necessary permission will be obtained for posting/airing these (for example, permission to post a flyer on a bulletin board).
4. If recruitment material is being mailed or otherwise distributed, submit the proposed material and describe where/how the distribution list will be obtained:       or  N/A
5. Describe how the recruitment methods described will be effective in attracting the targeted subject population: The target population is patients who recently underwent or are scheduled to undergo an echocardiogram and/or right heart catheterization. By screening patients scheduled for these tests we will be able to efficiently identify potential subjects for recruitment.

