## F.2 Procedures

1. If **Yes**, respond to all of the following:
2. *Describe the scientific, methodological, and medical reasons to use a placebo:*
3. *Describe the care that will be given to subjects who receive placebo. If this is local standard of care, specify that:*
4. *Describe all potential risks to the placebo group and how the risks will be minimized.*
5. *Summarize the research design and sequentially identify all procedures to be performed to accomplish the specific aims of the project. Clearly identify and distinguish procedures that are considered experimental, procedures that are performed exclusively for research purposes (including “extra” routine tests), and procedures that would occur regardless of the research (i.e., standard of care). Point out any procedures, situations, or materials that may be hazardous, and the precautions to be exercised to maintain subject safety:*

This is a prospective cohort study. Consecutive patients cared for at Tufts Medical Center, who have had a recent (within 30 days), or are scheduled to have a subsequent TTE performed at the discretion of the treating team will be screened for participation. Also, patients who are undergoing a right heart catheterization for a clinical indication will also be eligible for recruitment.

We will prospectively collect baseline clinical and demographic characteristics at the time of enrollment. We will be accessing the electronic medical record (Sorian) and entering the information collected into RedCap. There will be no collection of data beyond the date of enrollment, with the exception of those patients whose TTE or right heart catheterization has yet to be performed, in which case the subsequent TTE/right heart catheterization report will be the only information collected prospectively beyond the day of enrollment. The specific procedures to be followed will be:

- Patients who have had a recent TTE (within 30 days), or are scheduled to have a TTE and/or right heart catheterization performed for clinical reasons are eligible to participate in this study.
- If agreeable to participate in the study then participants will receive the usual standard of care (right heart cath and/or TTE) as dictated by the treating medical team.
- Upon signing the consent form, the research team will begin to collect baseline clinical and demographic information about participants from them and/or their medical chart.

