- Participants will then undergo the KOSMOS ultrasound evaluation at the time of enrollment or the earliest convenient time after enrolling in the study.
- The TTE and/or right heart catheterization data will be collected and compared with the results of the KOSMOS ultrasound.

*Please also describe the following concerning procedures:*

- - - - 1. How individuals will be screened for eligibility. Specify screening that will take place prior to informed consent and screening that will take place after informed consent:

Screening will begin through identifying individuals who are scheduled to undergo transthoracic echocardiogram and/or right heart catheterization at Tufts medical center. Patients who have recently underwent an echocardiogram may also be included if they are identified by the study team as potentially eligible for participation. There will be no additional screening prior to consent. Following consent the patient’s medical history will be evaluated by questioning the patient and, when necessary, reviewing the patient’s medical records for exclusion criteria. If no exclusion criteria are identified at this point then the patient will begin the protocol as described above.

- - - - 1. Procedures being performed to monitor subjects for safety or to minimize risks:

All data collected will be documented in the case report form in RedCap, which is stored on the Tufts secure server.

- - - - 1. All drugs and devices used in the research, their regulatory approval status, and the purpose of their use:

The KOSMOS device used in this project is an FDA approved ultrasound device that is available for commercial sale. It will be used to perform the bedside cardiac ultrasound as discussed above.

- - - - 1. The source records that will be used to collect data about subjects. (Attach all surveys, scripts, and data collection forms.):

See attached RedCap CRF

1. Is there a placebo control arm?

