**Yes  No**

If **Yes**, respond to all of the following:

1. *Provide the rationale for the waiver:* In order to identify patients eligible for enrollment the study team will need to determine which patients are scheduled to undergo an echocardiogram and/or right heart catheterization. To determine this the study investigators will need to be able to review the list of patients scheduled for these investigations.
2. *How the waiver or consent alteration will* ***NOT*** *adversely affect the rights and welfare of subjects:* The investigators will only review the patients to determine eligibility. They will not review any clinical or demographic data apart from that necessary to determine eligibility.
3. *How the research could* ***NOT*** *practicably be carried out without the waiver or alteration:* Without the waiver of consent the research team would not have a viable method of identifying partipicants eligible for enrollment in the study.
4. *How, subjects will be provided with additional pertinent information after participation. If subjects will not be provided this information after participation, explain why:*  The patients deemed eligible for enrollment will be approached by the investigators to request study participation. All details pertaining to the study will be provided at that time and informed consent will be performed prior to inclusion in the study.

If **Yes**, respond to all of the following:

1. *Provide the rationale for the waiver:*
2. *How the waiver or consent alteration will* ***NOT*** *adversely affect the rights and welfare of subjects:*
3. *How the research could* ***NOT*** *practicably be carried out without the waiver or alteration:*
4. *How, subjects will be provided with additional pertinent information after participation. If subjects will not be provided this information after participation, explain why:*
   1. Is a waiver of the consent process being requested for parents for research involving children?

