## K.2 Registration

1. *Describe the steps the research team will take to ensure that a subject is appropriately enrolled or registered in the study prior to receiving any study intervention (e.g. describe and submit any protocol eligibility checklist that will be used, specify who on the research team will confirm eligibility and that consent was documented, etc.):* As noted above the investigator and co-investigators will determine subject eligibility through review of the echocardiography and right heart catheterization schedules. Once patients are identified the patients will be approached regarding their interest in participation in the study. The step by step procedures to be followed have been outlined in the informed consent form.

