## K.3 Resources Available

1. Describe the roles/tasks of each research team member here (or alternatively, you may submit any current Delegation of Authority Log you may have which already has this information completed):

All research team members will participate in subject screening, enrollment, consent, data collection, and performing bedside ultrasound examinations.

1. Describe the qualifications (e.g., training, experience) of the PI and research team to perform their roles. Provide enough information for the IRB to determine the PI and research team are qualified to conduct the proposed research. Alternatively, you can submit the current CVs for the research team instead:

[name] is a board certified cardiologist and an Associate professor of medicine at Tufts University with an extensive background in clinical and non-clinical research. Drs. [name] and [name] are board certified in cardiology and pulmonology/critical care, respectively, and are currently completing advanced clinical fellowship training at Tufts, They have both been involved in the design and implementation of multiple retrospective and prospective clinical studies.

1. Describe the coverage plan to address any issues (including subject safety issues) that occur while the PI is away and/or unavailable. The research team member designated to serve as the acting PI in the PI’s absence should have similar training and expertise as the PI: [name] will serve as the acting PI should any issues arise when [name] is unavailable.
2. Describe the process to ensure the research team members have adequate oversight and are adequately trained regarding the protocol, study procedures, and their roles and responsibilities: The research team includes the investigator and two co-investigators. All three members of this team participated in developing the research question and protocol. They are all fully aware of the research protocol, study procedure, and their roles. If any amendments to the protocol are made all three members of the research team will be informed prior to said amendments. All research team members have confirmed their participation in the study and have agreed to remain up-to-date with any changes in the study protocols and/or procedures.
3. Medical or psychological resources that subjects might need, such as for emergencies or medical issues, are available for the study: Yes  N/A

##

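### The LVEF cohort is described as consecutive, but physician referral and permissive inclusion of patients with a recent TTE mean that this is not assured

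*Protocol*

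**What the plan says.** The design summary in Section F.2 states the sampling scheme for the TTE patients: "Consecutive patients cared for at Tufts Medical Center, who have had a recent (within 30 days), or are scheduled to have a subsequent TTE". Patients having a right heart catheterization are added in the next sentence as eligible for recruitment, without the word consecutive.

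Three other places describe how patients are found:

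- Section D.4.1: "Methods that will be used to identify potential subjects: Physician referral and chart review".
- Section F.2, in the answer on screening, for patients whose TTE is already done: "Patients who have recently underwent an echocardiogram may also be included if they are identified by the study team as potentially eligible for participation".
- Section K.2: the investigator and "co-investigators will determine subject eligibility through review of the echocardiography and right heart catheterization schedules".

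Two further statements bear on selection. Section G.2 limits what the investigators read before consent: "They will not review any clinical or demographic data apart from that necessary to determine eligibility". Section K.3 says who does the work: "All research team members will participate in subject screening, enrollment, consent, data collection, and performing bedside ultrasound examinations".

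The Objectives section sets the target of inference as the accuracy of "automated LVEF, stroke volume, and cardiac output detection in a real-world, clinical setting".

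**The concern.** A consecutive series is a claim about how patients enter the cohort: everyone who meets the entry condition in a given place and period is considered, and nobody chooses among them. In a study of diagnostic agreement, this claim is what lets the results be read as applying to ordinary practice.

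Physician referral does not have that property unless every eligible patient is referred, and the protocol does not require this. The wording for patients with a completed TTE is permissive and names no list from which they are drawn. For this group the reference result already exists when the patient is approached. The people who screen and enrol are also those who perform the index scan.

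The stake is the primary outcome. If the patients who come through these routes differ from the rest in how easily they are imaged, or in how closely the device tracks TTE, then the mean difference and limits of agreement describe a selected group while the report calls it consecutive. Any selection would carry into the pooling with the outside institution described in Section M. That section justifies pooling partly by generalizability, and route of identification is not among the variables it lists for sharing.

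**Working it through.** **1. The plan's own figures.** Section I.2 gives 73 evaluable patients for LVEF (95% agreement, 5% margin) and 35 for stroke volume and cardiac output (90% agreement, 10% margin). The single-proportion precision formula is n = z² × p × (1 − p) / d². The confidence level is not stated, so two-sided 95% is assumed (z = 1.96).

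- LVEF: 1.96² × 0.95 × 0.05 / 0.05² = 72.99, rounded up to 73.
- Catheterization: 1.96² × 0.90 × 0.10 / 0.10² = 34.57, rounded up to 35.

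Both reproduce. The formula has no term for how patients are sampled, so this point changes no stated number. Equally, recruiting more patients would not remove a selection effect.

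**2. The routes set against the claim.**

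| Route | Where | Does the text ensure that all eligible patients are reached? |
|---|---|---|
| Echo and catheterization schedules | F.2, K.2 | It can, if the whole list is worked through |
| Chart review | D.4.1 | It can, if applied to a complete list; none is named |
| Physician referral | D.4.1 | No |
| TTE already done, identified by the team | F.2 | No: permissive wording, no list, no rule to approach all |

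The F.2 summary applies the word consecutive to patients with a recent TTE as well as to those with a scheduled one. A schedule of coming tests would not by itself find the recent-TTE group. So the part of the cohort that most needs a defined list has none. The conflict concerns the LVEF component only, because the catheterization patients are not called consecutive.

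**3. Does another provision restore the property?** The limit in G.2 governs what is read before consent, not who must be approached. F.2 places the check of exclusion criteria after consent, which narrows the opportunity to select but does not require full approach. Section I.2 analyses all enrolled patients apart from those found to have moderate or greater regurgitant valve disease. That cannot correct selection that happened before enrolment.

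**4. What selection could do to agreement (illustration; every input is assumed).** Let a share f of patients come by discretionary routes. Let the standard deviation (SD) of the LVEF differences be s₁ in other patients and s₂ in these, with zero mean difference in both. The half-width of the 95% limits of agreement is then 1.96 × √[(1 − f)s₁² + f s₂²]. Take s₁ = 8 points, so that an unselected series gives 1.96 × 8 = 15.7.

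- Easier patients, s₂ = 5 to 6: at f = 0.25, 1.96 × √54.25 = 14.4 to 1.96 × √57 = 14.8. At f = 0.50, 1.96 × √44.5 = 13.1 to 1.96 × √50 = 13.9.
- Harder patients, s₂ = 10: at f = 0.25, 1.96 × √73 = 16.7. At f = 0.50, 1.96 × √82 = 17.7.

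The documents supply none of f, s₁ or s₂, and do not say which case is nearer the truth.

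**The case against.** The strongest reply is that this is loose wording, not a flawed sample. The core route is systematic, since screening starts from the echo and catheterization schedules. Chart review is compatible with consecutive screening. The sentence on patients with a completed TTE can be read as saying that they too are admissible, not that the team may choose among them. Much of this stands. It is not true that none of the routes is consecutive, and the right heart catheterization patients are outside the contradiction. What it does not answer is physician referral, and the absence of any list or approach rule for the recent-TTE group.

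A reader might infer more than the text supports:

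- *That the site can follow the plan and still pass over patients with poor windows.* Section G.2 confines review before consent to what eligibility needs, and image quality is not an eligibility criterion. Choosing on windows would depart from the plan.
- *That the results will look too good.* Referral could as well bring in difficult patients, and recruitment includes intensive care units. The direction is open.
- *That 73 of 130 is an expected usable-scan rate from which an inflated rate can be computed.* Section I.2 sets 130 to cover both inadequate windows and valve disease found on formal TTE. It is a recruitment cushion, not a forecast.
- *That no log of screened patients is kept.* The check box in Section G.5 cannot be read, so this cannot be said.

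Acquisition success is also not a named endpoint in Section I.1. The main consequence therefore lies in agreement, and the share of usable scans is supporting information.

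**Conclusion.** The point holds as a contradiction in the current text. F.2 promises a consecutive series of patients with a recent or scheduled TTE, while D.4.1 and the screening answer in F.2 describe routes that do not ensure one. The LVEF sample is therefore not assured to be consecutive, and selection before enrolment could bias agreement and the share of usable scans relative to accuracy "in a real-world, clinical setting".

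The documents fix neither the sign nor the size of the bias. Under the assumptions in the working, with a quarter to a half of patients from discretionary routes, the half-width of the limits of agreement runs from 13.1 to 17.7 points around an unselected 15.7. That range shows sensitivity and is not an estimate. The conclusion rests on the wording of the sections, not on these figures. It does not show that the study cannot meet its aim. It shows that a stated design property needs to be either secured or withdrawn.

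**What to change.** Choose one of two changes.

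**Make the series consecutive.** In D.4.1 and F.2, define the list: the echo schedule plus a list of patients with a TTE in the past 30 days, on days when an investigator is available. Approach patients in list order, remove the referral route, and record the reason for each patient not approached. The cost is slightly slower recruitment. Limiting the list to investigator days matters because the same three people consent and scan, and Section G.6 puts research activity at about 30 minutes per participant.

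**Or relabel the sample.** Keep the routes and replace the word consecutive in F.2 with convenience sample. Add a field for route of identification. As a sensitivity analysis, report agreement and the share with a usable automated value separately for schedule-identified patients and for referral- or team-identified patients. The cost is a weaker design label and one extra data field.

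The protocol does not say how far recruitment has gone. If it is complete, only the second change is still open.

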**Yes  No**

Describe the following concerning pregnancy testing and birth control:

- - 1. What type of pregnancy testing and how frequently will be conducted on women of reproductive potential. If testing will not be conducted provide the reason: NA
    2. What birth control methods **women** of reproductive potential will be instructed to use. If women will not be instructed about acceptable methods of birth control, clarify why: NA
    3. What birth control methods **men** of reproductive potential will be instructed to use. If men will not be instructed about acceptable methods of birth control, clarify why: NA
  1. Describe the data that will be collected during the study and how the data will be obtained:

Following identification of the study cohort (as described above), clinical data will be abstracted from the electronic medical record (Sorian) including: demographic characteristics (i.e. sex, age, height, weight, body mass index), cardiac risk factors (i.e. hypertension, diabetes, smoking, hyperlipidemia, previous myocardial infarction, previous cardiac intervention, previous strokes, heart failure, etc.), past medical history, indication for FoCUS assessment and TTE.

- - 1. If there are plans for long-term follow-up (once all research related procedures are complete), describe the data will be collected during this period:       or  N/A
  1. Specify which tests are routinely performed for clinical care, but are providing data for the research, and which tests are only performed for research purposes:

All of the formal echocardiogram and right heart catheterization tests are performed for clinical care. The bedside cardiac ultrasound is also performed to guide clinical care, primarily through its ability to provide real-time results at the time of patient evaluation. However, in the case of participants who present for an outpatient right heart catheterization and/or echocardiogram, the bedside ultrasound would not be performed for clinical care, rather, in this group of participants, the bedside ultrasound would be performed specifically for research purposes.

- 1. For Humanitarian Use Device (HUD) uses provide a description of the device, a summary of how you propose to use the device, including a description of any screening procedures, the HUD procedure, and any patient follow-up visits, tests or procedures.      or  N/A

